### Behavioral therapies for insomnia

Stimulus control therapy is a behavioral treatment for the management of chronic insomnia. It aims to assist persons with insomnia to re-associate the bed and the bedroom with falling asleep or back to sleep, and to acquire a consistent sleep pattern. This therapy entails specific instructions that focus on developing new sleep habits, such as avoiding activities (e.g. reading, watching TV, and worrying) in bed, getting out of bed if unable to fall asleep or back to sleep within 15–20 min and engaging in quiet activities until sleepy, going to bed only when sleepy, and waking up at the same time everyday.

Sleep restriction therapy consists of limiting the amount of time spent in bed to a specific sleep time. Sleep time is individualized, based on the persons’ total sleep time identified by reviewing the daily sleep diary kept at pretest. A sleep-wake schedule is planned to fit the persons’ lifestyle. The sleep-wake schedule is changed to accommodate improvements in the persons’ sleep, over time.

Both treatments are given by Master’s prepared therapists, trained in the implementation of the behavioral therapies. The sessions are offered in a small group (4–6 persons) format, based on availability of participants and to avoid any delay in treatment receipt. The treatments are delivered in the same dose: two sessions of 90 min each, once every 15 days, over a 4-week treatment period.

The results of two systematic reviews consistently demonstrated the effectiveness of stimulus control therapy and sleep restriction therapy [25, 31]. The treatments’ effects were reported in the short (1–3 months), intermediate (6 months), and long (≥12 months) term follow-up [25].

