**Methods/Design:**

A partially randomized clinical or preference trial is used. Eligible participants are randomized to two trial arms. First is the random arm involving random assignment to treatments, and second is the preference arm involving allocation to the chosen treatment. Participants with chronic insomnia are targeted. Two behavioral treatments are offered, stimulus control therapy and sleep restriction therapy, in the same format (small group) and dose (two sessions given over a 4-week period). A participant log is used to collect data on attrition. Adherence is evaluated in terms of exposure and enactment of treatment. Sleep-related outcomes (sleep parameters and perceived insomnia severity) are measured at pretest, posttest, 6 and 12 month follow-up. Treatment preferences, adherence and outcomes are assessed with reliable and valid measures.

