The sample size is estimated to attain adequate power to determine the effects of treatment preferences on attrition, adherence, and sleep outcomes. Sample size estimation also considers the repeated measure feature of the design. Within-subject designs require a smaller number of participants than between-subject designs, to achieve the same statistical power [30]. A medium sized effect (0.5) is anticipated on the basis of: 1) results of a systematic review showing that behavioral therapies had moderate-to-large effects on sleep parameters (sleep onset latency and wake after sleep onset) in middle-aged and older adults [31]; and 2) an expected medium effect for the comparison of participants assigned to treatment randomly or congruent with their preferences. A medium effect is anticipated, rather than a small effect as reported in the literature, with the use of a reliable and valid measure of treatment preferences. Applying Cohen’s [32] criteria for an anticipated medium effect size for the main comparison, the inclusion of four groups (i.e. participants allocated to the stimulus control therapy and those allocated to the sleep restriction therapy either randomly or based on their preference), and setting α at .05 and β at .80, the required sample size is 60 per group, for a total of 240 participants to be recruited.

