### Data analysis

In addition to descriptive statistics to characterize the participants in terms of their demographic and clinical characteristics, the following analyses are planned to address the study objectives:Objective 1: Chi-square test will be used to compare the number of participants who withdrew from the study across the four study groups defined by the type of treatment received (stimulus control therapy and sleep restriction therapy) and the method of allocation to treatment (random and preference). One-way analysis of variance will be applied to examine differences in level of adherence (i.e. attendance to treatment sessions and enactment of treatment recommendations), and the pattern of change (estimated with a slope) in the sleep outcomes, across groups.Objective 2: Chi-square test will compare the number of dropouts between participants in the random arm who receive matched and mismatched treatment. Independent samples t-test will examine differences between the matched and mismatched subgroups in levels of adherence (exposure and enactment) to treatment and the pattern of change in the sleep outcomes.

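### Therapy is given in small groups, but the planned tests and the sample size ignore therapy-group clustering; the four-group ANOVA is anti-conservative for any positive intracluster correlation

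*Protocol article*

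**What the plan says.** Under Behavioral therapies for insomnia, both treatments are given by trained therapists in two 90-minute sessions: "The sessions are offered in a small group (4–6 persons) format, based on availability of participants". The abstract confirms that the two therapies are delivered "in the same format (small group) and dose (two sessions given over a 4-week period").

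Under Data analysis, Objective 1 compares four groups formed by therapy and method of allocation. It uses a chi-square test for withdrawals, and for the rest: "One-way analysis of variance will be applied to examine differences in level of adherence", with the same test for slopes of the sleep outcomes. Objective 2 compares matched and mismatched participants in the random arm by chi-square and independent-samples t-test. No test has a term for therapy group or therapist.

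Under Sample, the size calculation rests on these statements: "A medium sized effect (0.5) is anticipated on the basis of" earlier evidence; "the inclusion of four groups"; "setting α at .05 and β at .80"; and the result, "the required sample size is 60 per group, for a total of 240 participants to be recruited". The paragraph mentions repeated measures but gives no ICC, design effect or therapy-group term. The Discussion raises unequal group sizes, unequal variances and baseline imbalance, but not clustering. Nowhere does the article say whether a session may hold participants from both the random and the preference arm.

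**The concern.** People who attend the same sessions share a therapist, peers, a discussion and a calendar period. Their attendance, enactment and sleep outcomes may therefore be correlated. Chi-square tests, one-way ANOVA and the t-test cannot allow for this.

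Two things are at stake. For any contrast nested in therapy groups, the usual standard error is too small and the p-value too low. Sixty people treated in about a dozen groups also carry less information than 60 independent people, so power for such contrasts is below what the calculation implies.

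Brevity of the article does not explain this. It names the tests, and those tests have no place for a group effect.

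**Working it through.** **Inputs from the article.** Therapy-group size 4 to 6 (midpoint m = 5 used); α = .05 (taken as two-sided); β at .80 read as power of .80; effect 0.5; four groups; 60 per group, 240 in total.

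**Assumptions.** The article gives no ICC, so values from .01 to .10 are shown. It does not say whether sessions mix allocation arms, so both cases are shown.

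**The plan's own figure.** Two groups, d = 0.5, two-sided α = .05 and power .80 need 63 per group (64 by the t distribution). At 60 per group the t-based power is 77.5%. A four-group ANOVA with Cohen's medium f = 0.25 needs about 179 in total (45 per group) and has 91% power at 240. Neither reading gives exactly 60. That is a separate matter, so both readings are carried forward.

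**Design effect.** DE = 1 + (m − 1) × ICC. For m = 5 and ICC = .05, DE = 1 + 4 × .05 = 1.20, effective n = 60/1.20 = 50, and the standard error is understated by a factor of √1.20 = 1.10.

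| Assumed ICC (m = 5) | DE | Effective n of 60 | Power, pairwise d = 0.5 | Power, ANOVA f = 0.25, N = 240/DE |
|---|---|---|---|---|
| 0 | 1.00 | 60 | 77.5% | 91% |
| .01 | 1.04 | 57.7 | 76% | 90% |
| .02 | 1.08 | 55.6 | 74% | 89% |
| .05 | 1.20 | 50.0 | 70% | 85% |
| .10 | 1.40 | 42.9 | 63% | 78% |

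The power columns apply to contrasts fully nested in therapy groups, that is, to single-arm sessions. With m = 4 or 6 the DE at ICC .10 is 1.30 or 1.50.

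**Type I error, single-arm sessions.** For the four-group ANOVA, a large-sample approximation is P(χ² on 3 df > 7.815/DE). This gives 6.5/8.9/13.4% at ICC .02/.05/.10. For one two-group contrast, 2 × [1 − Φ(1.96/√DE)] gives 5.9/7.4/9.8%.

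**Simulation.** 20,000 runs, no true difference, 60 per group, therapy groups of 5, nominal 5%:

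| Sessions | Test | ICC .02 | ICC .05 | ICC .10 |
|---|---|---|---|---|
| One arm only | Four-group ANOVA | 6.6% | 8.7% | 13.1% |
| One arm only | Random v preference within a therapy | 6.0% | 7.2% | 9.3% |
| Arms mixed | Four-group ANOVA | 5.5% | 6.2% | 7.4% |
| Arms mixed | Stimulus control v sleep restriction | 6.0% | 7.2% | 9.8% |
| Arms mixed | Random v preference within a therapy | 4.9% | 4.9% | 4.9% |

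Repeat runs of the ANOVA rows stayed within about 0.6 percentage points. The ANOVA exceeds 5% in both cases because its three degrees of freedom include the treatment contrast, and each therapy group receives a single therapy whichever arms it holds.

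**The case against.** The strongest reply is that the trial's main question may be almost untouched. The study is about allocation method, and groups were formed by availability and to avoid delay, which is compatible with mixing arms. If arms were mixed, the random-versus-preference contrast within a therapy holds its level at every ICC tried. Matched and mismatched participants given the same therapy could share sessions too, so Objective 2 is probably less exposed. This stands, subject to the mixing, which the article neither states nor excludes. It does not rescue the ANOVA actually planned for Objective 1.

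Second, no ICC is documented. At .01 the loss is one to two points of power, which is trivial. This stands too.

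Third, the power loss depends on the reading of the Sample paragraph. Its reference to four groups fits the ANOVA reading, where power is still about 85% at ICC .05. For the overall allocation effect (120 v 120, d = 0.5) power starts at 97% and is still 90% at ICC .10. The fall to 63% belongs to the pairwise reading with single-arm sessions and the largest ICC shown.

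Fourth, attrition is counted from consent. People who leave before joining a therapy group are not clustered, so the chi-square comparison of withdrawals is affected less.

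A reader might infer that every planned standard error and the stated power are simply wrong. The article does not support that: whether a given contrast is affected, and how much, depends on the unknown ICC and mixing. Nor does it show that a group identifier already exists. It says only that the therapist records who is present and that attended sessions are counted.

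**Conclusion.** The point holds in conditional form. The design creates clusters of 4 to 6, and neither the named tests nor the sample size allows for them. For any positive ICC the four-group ANOVA is anti-conservative: about 6.5/9/13% with single-arm sessions and 5.5/6/7.5% with mixed sessions, at assumed ICCs of .02/.05/.10 and groups of 5. The random-versus-preference contrast, and probably matched versus mismatched, is affected mainly if sessions were not mixed. The loss of power ranges from negligible at ICC .01 to about 14 points at ICC .10 (77.5% to 63% pairwise, 91% to 78% for the ANOVA). These figures rest on assumed ICCs, even groups of 5 and equal cells of 60. The Discussion itself expects that the preference arm may be unequal. The defect is moderate and worth correcting before analysis; it does not invalidate the trial.

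**What to change.** 1. State whether sessions held random-arm and preference-arm participants together.
2. Recover each participant's therapy group and therapist from the session records, and confirm that those records allow it.
3. Replace the ANOVA and t-tests with a linear mixed model with a random effect for therapy group and small-sample degrees of freedom. Report the treatment and random-versus-preference contrasts separately.
4. For attendance, and for attrition after group assignment, use GEE or cluster-robust standard errors. Participants assigned to a group who never attend stay in that group. Those who leave before assignment enter as unclustered singletons.
5. Restate power over a range of assumed ICCs, and say which effect-size reading is meant. Recruitment does not change.

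The study is still collecting 12-month data, so the cost is analysis wording and retrieval of group membership. The price is somewhat wider intervals for contrasts nested in therapy groups. With full, even groups there would be about 240/5 = 48 therapy groups, or 12 per cell, enough for such a model. An unbalanced preference arm could leave one cell with fewer, which is why small-sample degrees of freedom are needed.

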### Variables and measures

*Socio-demographic characteristics* of participants are assessed with standard questions gathering information on age, sex, marital status, level of education, employment status, and ethnicity.

*Clinical characteristics* relate to the type of insomnia (i.e. difficulty falling or staying asleep), whether the insomnia is primary (not associated with the onset of physical or mental health problems) or comorbid (associated with the occurrence of such problems), and duration of insomnia. These are assessed with relevant items of the Insomnia Interview Schedule developed and validated by Morin [28]. Participants also report on the presence of comorbid conditions (e.g. cancer, diabetes, cardiac disease) and on the type of treatment for managing these conditions, which could affect the experience of insomnia and the expressed preferences for insomnia treatment, and the effectiveness of treatment in managing insomnia.

*Preferences for treatment* are measured with an adapted version of the Treatment Acceptability and Preference scale [24]. It contains three sections. The first presents the description of one treatment. The description introduces the treatment’s name and goal; explains the activities comprising the treatment, the recommendations to be followed by the participants, the mode of delivery and dose of treatment; and summarizes evidence of the treatment’s benefits and risks. Information on benefits and risks is synthesized from available empirical literature, and presented in simple, non-technical, and easily understood terms. Following the description is a set of items for participants to rate the treatment relative to four attributes: 1) effectiveness in managing insomnia in the short and long term, and in improving daytime functioning; 2) appropriateness or suitability in addressing insomnia; 3) severity of side effects; and 4) convenience, that is, ease of implementing it in daily life. A five-point rating scale, ranging from *not at all* (0) to *very much* (4) is used. The second section of the Treatment Acceptability and Preference (TAP) presents the description of the alternative treatment, and the items for rating it. The third section includes two questions asking participants to indicate if they have a preference for any treatment and, if they do, the preferred treatment. In this study, the nine items rating the attributes of the two behavioral therapies are internally consistent (Cronbach’s alphas > .85) and valid, evidenced by significant associations between the treatments’ ratings and the expressed preferences. The order for presenting the treatment options is randomized to avoid an order effect.

*Attrition* is noted and documented in a log. The research assistants record the following information for each participant: completion of pretest measures, attendance at treatment sessions, completion of post-test, 6-month and 12-month follow-up measures, time at which the participant withdraw and reasons for withdrawal as reported by participants. Attrition rate will be computed as the percentage of participants who drop out of the study at any time after providing consent to take part in the trial.

*Two components of adherence to treatment* are examined: exposure and enactment. Exposure is operationalized as participants’ attendance at the planned treatment sessions. The therapist facilitating the sessions records the presence of each participant and the total number of sessions attended will be counted. Enactment represents the extent to which participants apply the treatment recommendations in daily life. It is assessed by having participants complete a checklist. The checklist was developed following the procedure described by Stein and colleagues [33]. It includes 13 items reflecting the behavioral treatments’ recommendations that are discussed during the sessions and that participants are expected to carry out on a daily basis. Examples of these recommendations include: avoiding caffeine and nicotine before bedtime, going to bed only when sleepy and waking up at a regular time. Participants indicate whether or not they implement each of the listed treatment recommendations on every day of the treatment and post-test periods. They return the completed checklist along with the daily sleep diary every morning. The percentage of treatment recommendations actually applied, averaged by week, will quantify enactment.

*Sleep outcomes* include sleep parameters and perceived insomnia severity. The sleep parameters are assessed with the daily sleep diary (DSD) completed for a week, at each data collection point and during the 4-week treatment period. The DSD is a self-administered log of nightly sleep behaviors, developed by Morin [28]. Participants report on bed time, time to fall asleep, number and length of each awakening, and wake up time. They complete the DSD upon awakening and are asked to return the completed DSD by either calling in their responses to a voice mail service or sending them by e-mail, each morning to decrease the possibility of retrospective estimates and recall bias. The DSD demonstrated test-retest reliability (r: .69–.93) and validity, evidenced by correlation with actigraphy values for the same variables [27]. Relevant DSD data will be used to quantify the following sleep parameters: sleep onset latency (i.e. time it takes to fall asleep), wake after sleep onset (i.e. time awake across all awakenings), total sleep time, and sleep efficiency (i.e. percentage of total time in bed actually asleep).

Perceived insomnia severity is measured with the Insomnia Severity Index (ISI). The ISI has seven items assessing distress with the sleep problem and satisfaction with sleep patterns. The ISI demonstrated acceptable internal consistency reliability (α ≥ .85) and validity as evidenced by correlation with other subjective and objective measures of insomnia severity [34].

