### Sample

Participants with insomnia are recruited through community media advertisements in local newspapers, radio station, and local newsletters targeting middle-aged and older adults. Flyers advertising the study are distributed to community health centers, hospital outpatient clinics, a leisure complex for older adults and sleep clinics.

Persons with insomnia are eligible for the study if they 1) are non-institutionalized adults (≥40 years of age) as insomnia is prevalent in middle-aged and older adults [26], 2) have the ability to read and write English, and 3) complain of difficulty initiating and/or difficulty maintaining sleep, manifested in sleep onset latency and/or time awake after sleep onset of 30 min or more per night, for a minimum of three nights per week, for a duration of at least 6 weeks [27], ascertained with relevant questions of the Insomnia Interview Schedule [28]. Individuals are excluded if they have: 1) cognitive impairment indicated by a score < 24 on the Mini-Mental State Exam [29] because cognitive impairment interferes with participants’ understanding of and ability to implement the behavioral therapies; and 2) confirmed medical diagnosis of sleep apnea as reported by participants; the behavioral therapies are not recommended for sleep apnea.

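### Objective 1 compares self-selected with randomized groups without adjusting for the comorbidity and comorbidity treatment that the plan says could affect both preference and treatment effect

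*Protocol article*

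**What the plan says.** In the protocol article, the clinical characteristics paragraph under Variables and measures has participants report their comorbid conditions and also "on the type of treatment for managing these conditions". It explains why these are collected: they are factors "which could affect the experience of insomnia and the expressed preferences for insomnia treatment, and the effectiveness of treatment in managing insomnia".

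The Data analysis section gives clinical characteristics one role, namely "descriptive statistics to characterize the participants in terms of their demographic and clinical characteristics". For Objective 1 it then names the tests. For attrition: "Chi-square test will be used to compare the number of participants who withdrew from the study across the four study groups", the groups being therapy received crossed with method of allocation. For adherence, and in the same sentence for the slopes of the sleep outcomes: "One-way analysis of variance will be applied to examine differences in level of adherence". No covariate appears in either.

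The Design section and the Discussion both say that comparing people who get the same therapy by chance or by preference shows what preference contributes. The Discussion also accepts, as its second challenge, that those who choose one therapy may differ from those who choose the other. Comparability between participants assigned randomly and by preference is then lost and the results may be confounded. The only statistical remedy it mentions concerns unequal variances.

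**The concern.** A baseline factor that may influence both which therapy a person chooses and how well therapy works is a confounder of any contrast involving a group formed by choice. The plan names such a factor, collects it, admits the resulting problem, and then fixes tests that cannot take it into account.

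The affected contrast is the one the design is built around. First-stage randomization makes the preference arm as a whole comparable with the random arm as a whole. It does not make the people who chose one therapy comparable with those randomized to that therapy. Analysing slopes instead of levels does not help, because the plan says the factor could affect effectiveness, and hence change over time. A difference between the chance and preference groups on one therapy could then be read as a preference effect when part of it reflects who chose that therapy.

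**Working it through.** **Plan figures.** The documents state no imbalance, no prevalence of comorbidity treatment and no size for its effect, so there is no plan figure to reproduce on this point. The only benchmark is the anticipated effect of 0.5 in the Sample section. The point does not depend on the sample size.

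**Step 1: which contrasts are exposed.** Assume 30% of participants carry the factor (for example, a relevant comorbidity treatment) and that carriers and non-carriers choose therapy A at different rates. For the preference arm:

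- share of carriers among choosers of A = 0.30 × P(A given carrier) / [0.30 × P(A given carrier) + 0.70 × P(A given non-carrier)], and correspondingly for B;
- both random-arm groups stay at 30% in expectation.

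| P(A): carriers / non-carriers | Preference group A | Preference group B | Gap from random group, A | Gap, B |
|---|---|---|---|---|
| 40% / 55% | 0.12/0.505 = 23.8% | 0.18/0.495 = 36.4% | −6.2 points | +6.4 points |
| 30% / 60% | 0.09/0.51 = 17.6% | 0.21/0.49 = 42.9% | −12.4 points | +12.9 points |
| 20% / 70% | 0.06/0.55 = 10.9% | 0.24/0.45 = 53.3% | −19.1 points | +23.3 points |

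Two contrasts stay balanced:

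- **Whole arm.** In the first row, 0.505 × 23.8% + 0.495 × 36.4% = 30%, equal to the random arm. The other rows give the same.
- **Matched versus mismatched in the random arm (Objective 2).** With 1:1 second-stage allocation, half of every preference subgroup is matched. The carrier share among matched participants is 0.30 × [0.5 × P(A) + 0.5 × (1 − P(A))] / 0.5 = 30%, where P(A) is the carriers' rate, whatever its value.

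Only the therapy-specific groups of Objective 1 are exposed.

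**Step 2: size.** Bias in a same-therapy contrast = difference in carrier share × effect of the factor in SD. With gaps of 6 to about 20 points:

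- effect 0.5 SD: 0.06 × 0.5 = 0.03 to 0.20 × 0.5 = 0.10 SD;
- effect 0.2 SD: 0.01 to 0.04 SD;
- effect 0.8 SD: 0.05 to 0.16 SD.

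The single largest gap in the table, 23.3 points, gives 0.12 SD at an effect of 0.5 SD.

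Against the planned 0.5, the central range is 0.03/0.5 = 6% to 0.10/0.5 = 20%.

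**Step 3: direction.** The gaps have opposite signs in the two therapies. The bias can therefore look like a preference effect that differs by therapy, and it can contribute to a significant four-group test even when preference does nothing.

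**The case against.** **Covariates belong in the analysis plan.** A protocol article often leaves covariates to a statistical analysis plan, which is not shown here. That would answer a complaint that covariates go unlisted. It does not answer this one: the article names the tests, and a chi-square test and a one-way ANOVA have no place for covariates. If a separate plan already adjusts, the article's wording should be brought into line with it.

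**The authors already disclose the problem.** They do, but disclosure changes no estimate, and the variables needed to reduce the bias are already collected.

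**The bias is modest and rests on assumed inputs.** This stands. Under mild selection it is about 0.03 SD, and values near 0.10 SD need strong selection. A reader might set the upper value against the smallest preference effect in the Background and get 0.10/.15 = 67%. That pairs the largest assumed bias with the smallest cited effect and is not a fair summary.

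**Stronger readings that the documents do not support.**

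- A reader might infer that sleep-aid use goes unrecorded. The diary summary lists "Participants report on bed time, time to fall asleep, number and length of each awakening, and wake up time", and the exclusions are cognitive impairment and "confirmed medical diagnosis of sleep apnea as reported by participants", so users of sleep aids are not excluded. But this is a condensed article, and the full diary is not shown. The insomnia characteristics are described only by "These are assessed with relevant items of the Insomnia Interview Schedule", without listing those items. Silence here does not show that the information is missing.
- A reader might see a contradiction in recording treatment for comorbid conditions only. There is none: the plan says comorbid conditions and their treatment could matter, and those are what it records. It makes no claim about concomitant treatment in general, and it says could affect, not does.
- A reader might extend the confounding to Objective 2. Under 1:1 allocation the matched and mismatched groups are balanced in expectation.
- A reader might want to exclude or adjust for people who add insomnia care after allocation. That would condition on something allocation may itself have caused, and could introduce bias.

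**Conclusion.** The point holds for the four-group comparisons of Objective 1. The plan identifies comorbid conditions and their treatment as factors that could affect both choice and treatment effect, concedes that the groups formed by choice may not be comparable, and fixes unadjusted tests across those groups.

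The illustrative size is 0.03 to 0.10 SD against a planned 0.5. It assumes 30% prevalence, choice rates differing between carriers and non-carriers by 15 to 50 percentage points, and a 0.5 SD effect of the factor. It also treats everyone in the preference arm as having a preference. Participants with none are assigned at random, which would dilute the imbalance. The direction of any real bias cannot be known from the documents.

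The finding concerns baseline adjustment in one objective. It does not say that the randomized whole-arm contrast is biased, that Objective 2 is confounded at baseline, or that sleep-aid use is unmeasured.

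**What to change.** In the Data analysis section, for Objective 1:

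- Replace the one-way ANOVA of adherence and outcome slopes with a linear model (ANCOVA) containing the four treatment-by-allocation groups and the baseline comorbidity and comorbidity-treatment indicators. Report the preference-minus-random contrast within each therapy.
- For attrition, replace the chi-square test with logistic regression on the same groups and covariates.
- Report the whole-arm contrast, preference versus random, alongside, keeping everyone in the arm given at the first stage. This matches the wording of Objective 1 and is protected by randomization. It answers a slightly different question, because the mix of therapies may differ between arms, so it complements the same-therapy contrasts and does not replace them.
- State that adjustment removes only measured confounding.

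In Objective 2 the same covariates may be added for precision, and should be described that way.

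The cost is small. No new data are needed, and the wording can be fixed before analysis because 12-month collection was still under way. The model spends a few degrees of freedom out of the 240 − 4 = 236 residual ones available before dropout. The indicators should be few and defined in advance, particularly for the attrition model if dropouts are few.
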